### Participants

Only patients with atrial fibrillation, above 18 years, and with TTR <50% based on the last three values of INR will be included in this study. Patients will be excluded if they have reached a stable dose of warfarin, liver dysfunction, alcoholism, use of another anticoagulant, use of chemotherapy, if they changed the dose of amiodarone 1 week before or if they do not meet the inclusion criteria.

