### Sample size

With a sample size of 150 patients for each arm separately, the study will have a power of 80% to observe a difference of 8% between TTR means of the TA and PA groups, using sigma of 25% and alpha of 0.05.

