### Laboratorial measures and questionnaires

Oral anticoagulant therapy will be assessed by the prothrombin time (PT) in an automated coagulometric method. Venous blood samples will be collected in tubes containing sodium citrate 3.8%. INR calculation will be obtained by the ratio PT of the patient/normal PT controls, elevated to the international sensitivity index. Besides current INR, past INR values will be checked in electronic medical records. TTR will be calculated by the Rosendaal method [36], which uses linear interpolation to assign an INR value to each day between successive observed INR values. Peripheral venous blood will be collected into a BD Vacutainer System® without anticoagulant for measurements of serum creatinine, alanine aminotransferase (ALT), and aspartate aminotransferase (AST) by colorimetric and enzymatic assays.

Physicians and pharmacists will also complete a questionnaire for each patient. These will include the following variables: name, age, sex, body mass index, smoking, weekly intake of alcoholic beverages, weekly intake of dark green vegetables, comorbidities, results of last INR values, adverse events, and other drug use. In addition, the physician will evaluate the patients with the CHADS_2_VASC_2_ and HAS-BLED scores [37–39]. The CHADS_2_VASC_2_ score estimates stroke risk in patients with atrial fibrillation. The variables are congestive heart failure, hypertension, age ≥ 75, diabetes mellitus, a history of stroke or transient ischemic attack symptoms and vascular disease history [37, 38]. The HAS-BLED score estimates the risk of major bleeding for atrial fibrillation patients on anticoagulation care. “HAS-BLED” is an acronym for Hypertension (uncontrolled, systolic blood pressure >160 mmHg), Abnormal liver (cirrhosis or bilirubin >2x normal or AST/ALT/alkaline phosphatase >3x normal) and renal function (dialysis, transplant, creatinine > 2.6 mg/dL), Stroke history, Bleeding predisposition or Prior Major Bleeding, Labile INRs (unstable/high INRs or TTR < 60%), Elderly (age ≥ 65), Drugs (antiplatelet agents, nonsteroidal anti-inflammatory) or alcohol usage (≥8 drinks/week) [39]. Each patient will have an individual record, which remains with the group of pharmacists and physicians. This record will provide information on current warfarin dose (mg/week), daily dose, and INR values. Furthermore, each patient will have a card to register the warfarin daily dose.

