### Statistical analysis

Statistical analyses will be carried out using SPSS software (v. 16.0, IBM, New York, NY) and the level of significance set at p ≤ 0.05. Pharmacoeconomic data will be evaluated using the TreeAge software (TreeAge, Inc., Williamstown, MA). Chi-square tests will be performed for comparative analysis of the categorical variables (such as adverse events, and evaluation of percentage of INR within therapeutic range) according to the polymorphisms or with the two approaches that will be made (TA and PA). Students’ *t*-tests or Mann-Whitney tests will be used for comparing TTR means and the time to achieve the therapeutic range according to the two groups. In addition, multivariate linear regression analysis will be used to identify variables associated with the TTR mean and with the time necessary to achieve the therapeutic range. A new randomization will not be performed for substitution of patients with missing data.

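### The between-arm TTR comparison leaves out baseline INR and baseline TTR, which are known for every patient: a loss of precision, not of validity

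*Protocol article*

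**What the plan says.** All references are to the protocol article.

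- **Treatment comparison.** Under Statistical analysis, Student's t-tests or "Mann-Whitney tests will be used for comparing TTR means" between the two groups. No covariate is named, and no rule is given for choosing between the two tests.
- **Regression.** The same section adds that "multivariate linear regression analysis will be used to identify variables associated with the TTR mean". This model is not named as the treatment comparison, and its covariates are not listed.
- **Baseline TTR.** Under Participants, patients with "TTR <50% based on the last three values of INR will be included in this study", so each one has a baseline TTR.
- **Baseline INR.** Under Trial design, the current INR guides the first dose in the TA group. In the PA group it is needed to recognise an algorithm dose that runs against the current INR. Under Laboratorial measures and questionnaires, "Besides current INR, past INR values will be checked in electronic medical records".
- **TTR construction.** TTR is calculated by Rosendaal linear interpolation at 4 and 12 weeks. The protocol starts at randomization, patients are told the new dose the next day, and the next INR is at day 7.
- **Sizing.** Under Sample size, 150 patients per arm give 80% power "to observe a difference of 8% between TTR means of the TA and PA groups", "using sigma of 25% and alpha of 0.05".

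**The concern.** A baseline measurement that predicts the outcome can absorb part of the patient-to-patient variation and so narrow the confidence interval for the treatment effect. Here a link is likely for two reasons. Baseline TTR and INR reflect the same patient's anticoagulation control. In addition, the day-0 INR, taken before any effect of the new dose, appears to enter the outcome itself through the interpolation of the first week. The stated design has no margin above 80% power, so precision that needs no extra data is worth having.

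A related point concerns the choice of test. The trial is sized on a difference in means, but one of the two permitted tests does not address that quantity. Mann-Whitney compares how the two distributions are ordered. It speaks to a mean difference only under further assumptions, such as a pure shift, which are doubtful for a percentage bounded at 0 and 100.

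**Working it through.** **1. The plan's own figure.** Inputs from Sample size: difference 8, SD 25, 150 per arm, alpha 0.05. Sidedness is not stated; two-sided is assumed.

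- Standard error = 25 × √(2/150) = 2.887 points.
- Power = Φ(8/2.887 − 1.96) = Φ(0.811) = 79.1%. The exact t-test gives 78.9%.
- For 80% power, n per arm = 2 × 25² × (1.96 + 0.842)² / 8² = 153.3, so 154.

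A one-sided test would give 87.0%, so the stated 80% corresponds to an unadjusted two-sided comparison, to within rounding.

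**2. Share of the window that touches the day-0 INR.** The article does not say outright that the TTR window opens at randomization. It follows from the day-0 start, the first later INR at day 7 and the Rosendaal method: days 0-7 cannot be interpolated without a day-0 value. That interval is 7/28 = 25% of the 4-week window and 7/84 = 8.3% of the 12-week window. The day-0 INR is only one of its two ends.

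**3. Power with adjustment.** If the baseline terms explain a share R² of the outcome variance, the residual SD is 25 × √(1 − R²), and power is Φ(8 / [residual SD × √(2/150)] − 1.96).

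| R² | Residual SD | SE (points) | Power |
|---|---|---|---|
| 0 | 25.00 | 2.887 | 79.1% |
| 0.005 | 24.94 | 2.880 | 79.3% |
| 0.05 | 24.37 | 2.814 | 81.2% |
| 0.10 | 23.72 | 2.739 | 83.2% |
| 0.20 | 22.36 | 2.582 | 87.3% |

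**4. What R² might be.** The article gives no figure, so R² is an assumption. INR series were simulated without dose titration, with weekly correlation 0.1-0.5 and with or without a lasting patient-level component. Baseline explained about 5-20% of the variance of 4-week TTR and 0.5-10% of that of 12-week TTR. These ranges illustrate and do not bound the answer. A model with strong lasting patient differences, in which dose adjustment halves each patient's deviation, gave 7-29% at 4 weeks and 3-35% at 12 weeks.

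**5. Form of the covariate.** Low and high INRs both lower TTR, so a single linear INR term would miss much of the relation. In-range status plus distance from mid-range captures it.

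**The case against.** The strongest reply is that nothing here is an error. Under 1:1 randomization the unadjusted t-test is unbiased, holds its type I error and matches the basis of the sample size. Covariate lists are often left to an analysis plan, which is not shown, and the planned regression could carry an adjusted arm effect. Entry is restricted to TTR below 50% from only three INRs, which narrows baseline TTR and makes it noisy. Weekly dose adjustment may also weaken the link between baseline and outcome. The gain could then be negligible: at a correlation of 0.1 (R² = 0.01), power is 79.5%, 0.4 points above the unadjusted figure. TTR is also called a secondary measure under Outcomes.

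Most of this stands. Two stronger readings are tempting, and the article supports neither. A reader might infer that chance imbalance in baseline INR biases the comparison or leaves it invalid; such imbalance is already counted in the unadjusted test's error rate. A reader might also infer that the pre-treatment INR determines a quarter of 4-week TTR. It supplies one end of that interval, and the day-7 value, taken after the dose change, supplies the other.

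What does not stand is that the point is merely left open. The article names the treatment comparison and names it without covariates, and it gives the regression a different aim. TTR is listed among the main outcomes under Trial design, and it is the endpoint on which the trial was sized. The choice between t-test and Mann-Whitney is a separate matter that naming the t-test alone would settle.

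**Conclusion.** The point holds as an efficiency improvement. The planned t-test is valid, but it leaves unused baseline data that every patient has. With the article's difference, SD and sample size, adjustment would raise power from 79% to about 81-87% if baseline explains 5-20% of the variance, which is plausible for 4-week TTR. For 12-week TTR, where 0.5-10% was assumed, power would be about 79-83%, so the gain there may be negligible. These figures assume a two-sided test, an SD of 25 at both time points and a baseline-outcome relation that the article does not state. That the day-0 INR enters TTR is an inference; it would fail if the window opened at day 7.

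Separately, leaving Mann-Whitney as an option permits an analysis that does not test the mean difference on which the trial was sized.

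**What to change.** In Statistical analysis, replace the choice of t-test or Mann-Whitney for TTR by one prespecified ANCOVA. It regresses TTR on arm, baseline TTR (from the last three INRs) and baseline INR, the latter entered as in range yes/no and as absolute distance from mid-range. Report the adjusted mean difference with its 95% CI at 4 and at 12 weeks, and keep the unadjusted t-test as supportive. State in the same place that the TTR window opens with the day-0 INR, if that is the intention.

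The cost is a sentence or two of analysis wording and about three degrees of freedom out of 300 patients. No new data are needed, and neither the conduct of the trial nor its sample size changes.

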## Discussion

This randomized study will include patients with low TTR from a cardiovascular tertiary hospital and it was designed to evaluate whether a population-specific genetic algorithm might be more effective than traditional anticoagulation for a selected group of poorly anticoagulated patients.

Previous clinical trials tested genetic-based algorithms in patients beginning warfarin therapy and found contrasting results [43]. However, no study to date has focused on this specific group of difficult to anticoagulate patients.

Our study has some potential limitations. First, although we will check the adverse effects during the study, we will not be able to analyze them with adequate statistical power. However, since these events may severely affect cost-effectiveness analysis they are contemplated in the study design. Second, we will use an algorithm modeled from a Brazilian cohort of patients and it will be applied in a specific group of patients of a tertiary referral hospital. Thus, applicability of our findings will need of external validity.

## Abbreviations

ALT: Alanine aminotransferase
AST: Aspartate aminotransferase
CAPES: Coordenação de aperfeiçoamento de pessoal de nível superior
CNPQ: Conselho nacional de desenvolvimento científico e tecnológico
EM: Extensive metabolizer
FAPESP: Fundação de amparo à pesquisa do estado de São Paulo
IM: Intermediate metabolizer
INR: International normalized ratio
PA: Pharmacogenetic anticoagulation
PM: Poor metabolizer
PT: Prothrombin time
QALYs: Quality-adjusted life year
REDCap: Research electronic data capture
TA: Tradicional anticoagulation
TTR: Time in the therapeutic range
